#### Note on central tumors

When the GTV tumor is within 2 cm of a central structure (e.g. heart, trachea), it will be considered a central tumor. In such a scenario, the dose constraints to central structures in Table 2 are often not achievable. These should be planned using the same approach as in the RTOG 0813 study, which determined the safe dose level of central tumors for a 5-fraction SABR regimen. In such an approach, the PTV coverage is not compromised, but the OAR dose is to be kept as low as possible. This applies to the esophagus, heart, great vessels, trachea, and ipsilateral bronchus. For the esophagus, great vessels, trachea, and ipsilateral bronchi, the non-adjacent wall of the structure limited to a maximum dose of 105% of prescription dose. In contrast, maximum doses from the above table for the spinal cord, brachial plexus, skin, and stomach are NOT to be exceeded.

### Constraints for lung parenchyma

The dose constraints to the lung are not iso-toxic, meaning that the risk of toxicity is highest with highest dose levels. The constraints below based are those used for 5-fraction SABR regimens in patients without ILD, meaning that with a higher number of fractions (e.g. 10, or 15), the risk of toxicity will decrease. The pulmonary constraints consist of 2 critical volume constraints, along with the R100, R50, D2cm and V20 (volume of lung receiving at least 20 Gy), all defined below.

Critical volume constraint for both lungs (right lung + left lung): a total critical volume of 1500 mL receives no more than 12.5 Gy. This value is calculated from the dose-volume histogram as the absolute volume of lung tissue receiving < 12.5 Gy. That volume must be at least 1500 mL.

The conformality and V20 constraints for this study will be those used for the RTOG 0813 study, reproduced in Table 3.

**Table 3 Tab3:** Conformality and V20 constraints, as per the RTOG 0813 protocol [16]

PTV Volume (cc)	Ratio of prescription isodose volume to the PTV bolume (R100)		Ratio of 50% prescription isodose volume to the PTV volume, (R50)		Maximum dose (in % of dose prescribed) @ 2 cm from PTV in any direction, (D2cm) (Gy)		Percent of Lung receiving 20 Gy total or more (V20)	
	Deviation		Deviation		Deviation		Deviation	
	None	Minor	None	Minor	None	Minor	None	Minor
1.8	< 1.2	< 1.5	< 5.9	< 7.5	< 50.0	< 57.0	< 10	< 15
3.8	< 1.2	< 1.5	< 5.5	< 6.5	< 50.0	< 57.0	< 10	< 15
7.4	< 1.2	< 1.5	< 5.1	< 6.0	< 50.0	< 58.0	< 10	< 15
13.2	< 1.2	< 1.5	< 4.7	< 5.8	< 50.0	< 58.0	< 10	< 15
22.0	< 1.2	< 1.5	< 4.5	< 5.5	< 54.0	< 63.0	< 10	< 15
34.0	< 1.2	< 1.5	< 4.3	< 5.3	< 58.0	< 68.0	< 10	< 15
50.0	< 1.2	< 1.5	< 4.0	< 5.0	< 62.0	< 77.0	< 10	< 15
70.0	< 1.2	< 1.5	< 3.5	< 4.8	< 66.0	< 86.0	< 10	< 15
95.0	< 1.2	< 1.5	< 3.3	< 4.4	< 70.0	< 89.0	< 10	< 15
126.0	< 1.2	< 1.5	< 3.1	< 4.0	< 73.0	> 91.0	< 10	< 15
163.0	< 1.2	< 1.5	< 2.9	< 3.7	< 77.0	> 94.0	< 10	< 15

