### Dosimetry

Treatment can be delivered using static beams (either 3D-conformal radiotherapy or intensity-modulated) or rotational therapy (volumetric modulated arc therapy, or Tomotherapy). Only photon (X-ray) beams of 10 MV or less produced by linear accelerators will be used.

For purposes of dose planning and calculation of monitor units for actual treatment, this protocol will require tissue density heterogeneity correction. Successful treatment planning will require accomplishment of all of the following criteria:
Prescription isodose surface: The prescription isodose surface will conformally cover 95% of the target volume (PTV), such that 99% of the PTV will also receive at least 90% of the prescription dose. (PTV D95% = 100% of prescription dose and D99% = 90% of prescription dose)Target dose heterogeneity: The dose at the prescription isodose surface must be between 60 and 90% (inclusive) of the dose at the normalization point of the plan. The prescription isodose surface is typically 80% of the dose at the normalization point, though the allowed range enables flexibility to optimize dose to organs at risk (OARs), especially the lung.High dose spillage (as per the RTOG 0813 [16] protocol):
Location: Areas with dose > 105% of the prescription dose should be located primarily within the PTV itself. The cumulative volume outside the PTV volume with dose > 105% of prescription dose should be no more than 15% of the PTV volume.Volume: Conformality of PTV coverage will be determined by the R100 (the ratio of the volume of the prescription isodose to the volume of the PTV), R50 (The ratio of the volume of 50% of the prescription dose isodose to the volume of the PTV), and D2cm (the maximum total dose over all fractions in Gray (Gy) to any point 2 cm or greater away from the PTV in any direction), as per Table 3.All critical organ dose-volume constraints in Table 2 must be respected. **Lung dose constraints may not be exceeded for any reason.**

**Table 2 Tab2:** Recommended dose constraints for non-lung organs. 5-fraction and 8-fraction constraints based on RTOG 0813 protocol [16], SABR-COMET protocol [17], and Timmerman et al [18]. Constraints for other fractionation schemes are derived using BED_3_

Structure		Number of Fractions		
		5	10	15
Spinal Cord (contoured as spinal canal)	Max	30 Gy	34.5 Gy	39.5 Gy
	< 0.25 cc	22.5 Gy	29 Gy	33 Gy
	< 1.2 cc	13.5 Gy	17 Gy	19 Gy
Esophagus	Max	35 Gy	43.5 Gy	50.5 Gy
	< 5 cc	27.5 Gy	35.5 Gy	41 Gy

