### Procedure if lung constraints cannot be met

**The lung constraints are critically important for this study.** If one or more of the lung constraints cannot be met, even after varying the prescription isodose surface percentage between 60 and 90%, PTV coverage must then be compromised. Target coverage may be reduced until 95% of the IGTV is receiving the 95% of the prescription dose, and 90% of the IGTV is receiving 99% of the prescription dose, with the PTV covered as well as possible while respecting lung constraints.

**If the lung dose constraints still cannot be met, the patient should be treated with a 10 or 15-fraction regimen.** Such patients treated with protracted regimens due to inability to meet dose constraints will not count toward the primary analysis, but should still be followed for toxicity and outcomes. Such patients will be reported as a separate cohort.

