## Abbreviations

2D: 2-dimensional
4D: 4-dimensional
AE: adverse event
AJCC: American Joint Committee on Cancer
BED: Biologically effective dose
CAPRI: Canadian Pulmonary Radiotherapy Investigators’ Group
CBCT: Cone beam computed tomography
CT: Computed tomography
CTCAE: Common Terminology Criteria for Adverse Events
CTD: Connective tissue disease
D2cm: Maximum dose at 2 cm from planning target volume as a percentage of prescription dose
DICOM: Digital Imaging and Communications in Medicine
DLCO: Diffusing capacity of the lungs for carbon monoxide
DSMC: Data safety monitoring committee
DVH: Dose-volume histogram
ECOG: Eastern Cooperative Oncology Group
EQ-5D-5 L: EuroQol 5-Dimensional 5-Level
ES-NSCLC: Early-stage non-small cell lung cancer
FACT-L: Functional Assessment of Cancer Therapy - Lung
FDG: Fluorodeoxyglucose
FEV_1_: Forced expiratory volume in 1 s
FVC: Forced vital capacity
GI: Gastrointestinal
GTV: Gross tumour volume
HRCT: High-resolution computed tomography
IAEA: International Atomic Energy Agency
ICH GCP: International Council for Harmonisation Guidelines for Good Clinical Practice
ICMJE: International Committee of Medical Journal Editors
IGTV: Internal gross tumour volume
ILD: Interstitial lung disease
ILD-GAP: Interstitial Lung Disease – Gender, Age, Physiology
IPF: Idiopathic pulmonary fibrosis
IRB: Institutional Review Board
ITV: Internal target volume
MIP: Maximal intensity projection
MRI: Magnetic resonance imaging
NSCLC: Non-small cell lung cancer
OAR: Organ at risk
OS: Overall survival
PA: Pulmonary artery
PET: Positron emission tomography
PTV: Planning target volume
PV: Pulmonary vein
QA: Quality assurance
QIPCM: Quantitative Imaging for Personalized Cancer Medicine
R100: Ratio of 100% prescription isodose volume to planning target volume
R50: Ratio of 50% prescription isodose volume to planning target volume
REB: Research Ethics Board
ROI: Region of interest
RTOG: Radiation Therapy Oncology Group
SABR: Stereotactic ablative radiotherapy
SAE: Severe adverse event
V20: Volume of lung receiving at least 20 Gy

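### D2cm, one of the binding lung constraints, is defined both in Gy and in percent, and two of its 22 limits in Table 3 have the inequality reversed (minor)

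*Protocol article*

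**What the plan says.** Three places in the protocol article say what D2cm is.

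- Dosimetry, under high dose spillage, defines it as "D2cm (the maximum total dose over all fractions in Gray (Gy) to any point 2 cm or greater away from the PTV" and refers to Table 3 for the limits.
- The Table 3 column header, under Constraints for lung parenchyma, reads "Maximum dose (in % of dose prescribed) @ 2 cm from PTV in any direction, (D2cm) (Gy)", so it carries both units.
- The abbreviation list has "D2cm: Maximum dose at 2 cm from planning target volume as a percentage of prescription dose".

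Table 3 has 11 PTV rows with two D2cm columns, None and Minor deviation. The None limits run from < 50.0 to < 77.0. The Minor limits run from < 57.0 to < 89.0 over the first nine rows, then read > 91.0 (126 cc) and > 94.0 (163 cc).

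D2cm is in active use. Constraints for lung parenchyma lists the pulmonary limits as two critical-volume constraints "along with the R100, R50, D2cm and V20 (volume of lung receiving at least 20 Gy)". Dosimetry adds, in bold, "Lung dose constraints may not be exceeded for any reason". If a lung limit is missed, the planner must first vary the prescription isodose and then give up target coverage: "even after varying the prescription isodose surface percentage between 60 and 90%, PTV coverage must then be compromised". If that also fails, the patient moves to 10 or 15 fractions, with this result: "Such patients treated with protracted regimens due to inability to meet dose constraints will not count toward the primary analysis".

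**The concern.** A constraint that may never be exceeded needs one unit and a direction. Here the definition in the body text, which a planner would follow, gives the unit that does not work, and the workable one appears in the abbreviation list. The two reversed signs turn an upper limit into a lower one for the largest targets, where lung dose is hardest to control.

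Two things depend on the limit. One is lung dose in patients chosen because their lungs tolerate radiation badly. The other is who is analysed: failing a lung constraint can lead to lost target coverage and, at the last step, to a protracted regimen outside the primary analysis.

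**Working it through.** **Inputs.** Prescription 50 Gy in 5 fractions, with 45 Gy as the lowest de-escalated dose (Dose/fractionation). D2cm limits from Table 3. The spillage rule in Dosimetry: "Areas with dose > 105% of the prescription dose should be located primarily within the PTV itself". PTV margin 0.5 cm (Volume definitions). Tumour size up to 5 cm (Inclusion criteria). Tumour excursion up to 1 cm under the ITV approach (Motion management).

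**1. Unit.** Each None limit under both readings, at 50 Gy:

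| PTV (cc) | None limit | Read as %: limit/100 × 50 Gy | Read as Gy: limit/50 | Minor limit as printed |
|---|---|---|---|---|
| 1.8 and 3.8 | 50 | 25.0 Gy | 100% | < 57 |
| 7.4 and 13.2 | 50 | 25.0 Gy | 100% | < 58 |
| 22 | 54 | 27.0 Gy | 108% | < 63 |
| 34 | 58 | 29.0 Gy | 116% | < 68 |
| 50 | 62 | 31.0 Gy | 124% | < 77 |
| 70 | 66 | 33.0 Gy | 132% | < 86 |
| 95 | 70 | 35.0 Gy | 140% | < 89 |
| 126 | 73 | 36.5 Gy | 146% | > 91 |
| 163 | 77 | 38.5 Gy | 154% | > 94 |

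The Minor limits read in Gy are 57/50 = 114% to 94/50 = 188%. The spillage rule puts 105%, or 1.05 × 50 = 52.5 Gy, as the level that should lie mainly inside the PTV. Seven of the 11 None limits (54 to 77) and all 11 Minor limits would exceed 52.5 Gy at a point 2 cm outside it. The Gy reading therefore conflicts with the same section of the protocol. The percent reading gives a usable limit at 50 Gy, and also at 45 Gy (0.50 × 45 = 22.5 Gy to 0.77 × 45 = 34.65 Gy).

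**2. Sign.** 11 rows × 2 columns = 22 D2cm entries, of which 2 use >. At 50 Gy the bands that fall in neither column as printed are:

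- 126 cc: 0.73 × 50 = 36.5 Gy to 0.91 × 50 = 45.5 Gy.
- 163 cc: 0.77 × 50 = 38.5 Gy to 0.94 × 50 = 47.0 Gy.

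Above those bands every value would count as a Minor deviation, without limit.

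**3. How many patients could meet the reversed signs.** This step rests on an assumption: a spherical tumour, a 0.5 cm margin and straight-line motion of length m. Then V = (4/3)πR³ + πR²m, and tumour diameter = 2(R − 0.5).

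| PTV row | Diameter, m = 0 | Diameter, m = 1 cm |
|---|---|---|
| 95 cc | 4.7 cm | 4.2 cm |
| 126 cc | 5.2 cm | 4.8 cm |
| 163 cc | 5.8 cm | 5.3 cm |

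In the other direction, a 5 cm tumour gives a PTV of 113 cc at m = 0, 127 cc at 0.5 cm and 141 cc at 1 cm. The 126 cc row is reached only by tumours near the size limit that also move, and the 163 cc row lies outside eligibility in this model. If centres interpolate between the 95 and 126 cc rows, which the article does not state, tumours from about 4.2 cm (m = 1 cm) or 4.7 cm (m = 0) are touched.

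**4. Does R50 already protect the lung?** For spherical volumes, r(V) = (3V/4π)^(1/3). The distance by which the 50% isodose lies inside the 2 cm shell is r(PTV) + 2 − r(R50 × PTV).

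- Widest, 1.8 cc, None: 2.75 − 1.36 = 1.39 cm.
- Narrowest, 163 cc, Minor: 5.39 − 5.24 = 0.15 cm.

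The distance is positive in all 11 rows for both columns. A symmetric plan that meets R50 is therefore already below 50% at 2 cm. R50 is a volume ratio, however, so it does not rule out spill in one direction, which is what a point maximum is meant to catch.

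**The case against.** The best defence is that nobody would be misled. Dosimetry can be read as describing a physical dose, naturally in Gy, whose limits Table 3 expresses as a percentage. The Gy reading is so loose that no planner would adopt it. The Minor limits rise steadily from 57 to 89, so 91 and 94 plainly continue as upper limits, and the None limits in those rows are intact. A static spherical tumour within eligibility never reaches either faulty row. Every plan is peer-reviewed locally, and each centre must submit a mock plan or show earlier accreditation before opening. Table 3 is taken from another trial's protocol, so the signs may be inherited.

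Most of this stands and sets the severity. The intended reading can be worked out, no misreading by a centre is shown, and the signs matter only if a Minor deviation counts as meeting the constraint, which the article does not say. What does not stand is that the text is consistent. The abbreviation list defines the quantity itself as a percentage, and the header carries two units for the same numbers. The unit problem covers every row, whatever the tumour size. Two inequalities point the wrong way wherever they came from.

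**Conclusion.** The inconsistency is real and minor. D2cm has two incompatible definitions and a header that prints both units. Percent is the only workable one, and the gap between the readings is a factor of two at 50 Gy (for example 25 against 50 Gy). Two of 22 limits are reversed and, as printed, set no ceiling.

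The practical effect is limited by the intact None limits, the R50, V20 and 1500 mL rules, and plan review. Loss from the primary analysis comes only after the isodose has been varied and coverage reduced. Sample size, power and alpha are not affected. The unit and sign findings rest on the printed text alone. The tumour sizes and the R50 backstop rest on the spherical geometry and on motion between 0 and 1 cm.

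**What to change.** 1. In Dosimetry, define D2cm as the largest dose at any point at least 2 cm from the PTV, expressed as a percentage of the prescribed dose, in line with the abbreviation list.
2. Delete the Gy label from the D2cm header in Table 3.
3. Change the two Minor entries to < 91.0 and < 94.0 after checking the source table.
4. It would help to add one sentence on whether a Minor deviation meets the lung constraint, unless the full protocol already says so.

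The cost is one definition, one header, two signs and at most one sentence. Centres need a notice only if the working protocol carries the same slips. A re-check of treated plans is optional: the article does not say D2cm values are recorded, so they would have to be computed from the dose distributions gathered under Central imaging collection.

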### Procedure if lung constraints cannot be met

**The lung constraints are critically important for this study.** If one or more of the lung constraints cannot be met, even after varying the prescription isodose surface percentage between 60 and 90%, PTV coverage must then be compromised. Target coverage may be reduced until 95% of the IGTV is receiving the 95% of the prescription dose, and 90% of the IGTV is receiving 99% of the prescription dose, with the PTV covered as well as possible while respecting lung constraints.

**If the lung dose constraints still cannot be met, the patient should be treated with a 10 or 15-fraction regimen.** Such patients treated with protracted regimens due to inability to meet dose constraints will not count toward the primary analysis, but should still be followed for toxicity and outcomes. Such patients will be reported as a separate cohort.

### Quality assurance

In order to ensure patient safety and effective treatment delivery, a robust quality assurance protocol is incorporated. The following requirements must be completed for each patient:
Prior to treatment, each patient’s contours and radiation plan must be peer-reviewed at the local centre. This can include review by one other radiation oncologist, or discussion at quality assurance (QA) rounds.OAR dose constraints may be only exceeded with approval of the PI. Prior to plan approval, the dose to each organ at risk must be verified by the physicist or treating physician.All dose delivery for intensity-modulated plans (including arc-based treatments) will be confirmed before treatment by physics staff.Online imaging (Cone-beam CT, megavoltage CT or orthogonal KV with tumor tracking) will be used to verify patient positioning for each treatment. Ideally, direct tumour localization should be performed. For gated SABR treatments, direct tumour localization will be performed by matching the tumour position with the region of interest (ROI) defined by IGTV_CBCT. This will be followed by a gated 2-dimensional (2D)-kV in the anterior-posterior plane to verify the gating window. In the absence of direct tumour localization, reliable soft tissue surrogates are recommended. For non-gated radiotherapy, it is expected to match the image of the tumor with the ROI defined by the ITV.

### Quality Assurance for Centres Joining Study

Prior to opening the study, each participating research centre will be required to send to one of the Principal Investigators a mock treatment plan, to ensure that the treatment plans are designed in compliance with the protocol. The principal investigators will provide pertinent CT datasets. Centers that have previously been accredited for other trials (e.g. NRG Oncology, CAPRI, LUSTRE [20] or SABR-COMET [17]) must only send documentation of that accreditation.

## Adverse events

### Definitions

*Adverse Event (AE)* or reaction, as per definitions by the Common Terminology Criteria for Adverse Events [21], is any unfavorable and unintended sign (including an abnormal laboratory finding), symptom, or disease temporally associated with the use of a medical treatment or procedure that may or may *not* be considered related to the medical treatment or procedure.

*Serious Adverse Event (SAE)* or reaction as defined in the International Council for Harmonisation (ICH) Guideline: Clinical Safety Data Management: Definitions and Standards for Expedited Reporting, Section 2B [22] includes any untoward medical occurrence at any dose that:
Results in deathIs life-threatening (refers to an event in which the patient was at risk of death at the time of the event; it does not refer to an event which hypothetically might have caused death if it were more severe.)Results in persistent or significant disability/incapacityRequires in-patient hospitalization or prolongation of existing hospitalizationIs a congenital anomaly/birth defect

Important medical events that may not be immediately life-threatening or result in death or hospitalization may be considered a serious adverse event, when, based upon medical and scientific judgment, they may jeopardize the patient or may require intervention to prevent one of the other outcomes listed in the definition above.

*Unexpected adverse event* or reaction is one that the nature and severity is not consistent with the applicable product information (e.g., Investigator’s Brochure or Product Monograph, described in the research ethics board (REB)/institutional review board (IRB) approved research protocol or informed consent document), or occurs with more than expected frequency.

### Radiation therapy adverse events

RT delivered in this protocol can adversely affect organs at risk, most notably lungs, airway, esophagus, pulmonary vessels, and heart/pericardium, as these organs may be in close proximity to the intended target (PTV) of RT.
Cardiac and pericardial injury: though cardiac/pericardial toxicity is rare following conventionally-fractionated RT, such toxicity may be seen with SABR due to larger fraction sizes.Gastrointestinal/esophageal injury: SBRT can result in acute esophagitis and/or late esophageal stenosis or ulceration, with esophageal perforation occurring in the extreme cases.Central airway/bronchial injury: this injury may result in focal atelectasis and impair overall pulmonary status. Atelectasis can render assessment of tumor response very difficult. Investigators are referred to the strict criteria for progressive disease in the Disease Response and Progression section of this protocol to avoid such mis-characterization.Lung injury: radiation pneumonitis is a subacute inflammation of the end bronchioles and alveoli due to radiation exposure. Radiation fibrosis is a late manifestation of radiation injury to the irradiated lung. Radiation-induced lung injury has not been traditionally been a dose-limiting factor for SABR in healthy lung, though the risk seems to be significantly increased in patients with co-existing fibrotic ILD. Radiation pneumonitis can also be confused with other causes of respiratory deterioration including pneumonia, acute exacerbation of COPD, acute exacerbation of ILD and tumor recurrence. It is crucial for a Radiation Oncologist participating in this study to be aware of the potential differential diagnosis, as the symptomatology of radiation pneumonitis can mimic these other causes with fatigue, fever, shortness of breath, nonproductive cough, and a pulmonary infiltrate on chest radiography. For radiation pneumonitis, the infiltrate on chest radiography should include the area treated to a high dose of radiation but may extend outside of these regions. The infiltrates may be characteristically “geometric” though with modern radiotherapy techniques the region is likely to be ill-defined.

### Causality of pre-specified toxicity endpoints

Any Grade 3–5 toxicity listed in Table 4 will **automatically** be considered to be possibly, probably or definitely related to treatment, unless there is clear evidence that the adverse event is unrelated or unlikely to be related. The latter instance may occur, for example, in the case of a cardiac event in a patient with an upper lobe tumor and negligible heart dose, or esophageal issues in a patient who received negligible esophageal dose. The final decision will be made by the members of the data safety monitoring committee (DSMC). See below for causality definitions.

**Table 4 Tab4:** Pre-specified adverse events

Structure	Adverse Event
Cardiac and Pericardial	• Acute coronary syndrome
	• Aortic valve disease
	• Atrial fibrillation
	• Atrial flutter
	• Atrioventricular block
	• Conduction disorder
	• Constrictive pericarditis
	• Heart failure
	• Left ventricular systolic dysfunction
	• Myocarditis
	• Pericardial effusion
	• Pericardial tamponade
	• Pericarditis
	• Cardiomyopathy
	• Cardiac disorders-others
Gastrointestinal	• Dyspepsia
	• Dysphagia
	• Esophageal fistula
	• Esophageal hemorrhage
	• Esophageal necrosis
	• Esophageal obstruction
	• Esophageal stenosis
	• Esophageal perforation
	• Esophagitis
Pulmonary/mediastinal	• Atelectasis
	• Bronchial fistula
	• Bronchial obstruction
	• Bronchopleural fistula
	• Bronchopulmonary hemorrhage
	• Dyspnea
	• ILD or IPF exacerbation
	• Pneumonitis
	• Tracheal/Pulmonary fistula
	• Tracheal stenosis
	• Mediastinal hemorrhage
	• Pulmonary disorders-others

